### 9.5.2 Accompanying Research Analyses

Accompanying research will be conducted by the medical coordinator or his representatives. Analyses will be described separately.

## 9.6 Interim Analyses

No **interim analyses** regarding efficacy or futility are planned but 15-16 DSMB meetings will take place to assure and evaluate the safety.

## 9.7 Sensitivity Analyses

The primary analysis will be repeated for the PPS as **sensitivity analysis**.

In addition, the primary analysis will be repeated using a linear mixed model with age groups and treatment as fixed factors and site as random factor. Missing values will be replaced using multiple imputation using age groups and the 1-year value as exploratory variables.

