# 1. INTRODUCTION AND RATIONALE

## 1.1 Scientific Background

Tuberous sclerosis complex (TSC) is an autosomal dominant neurodevelopmental disorder affecting 1:6,760 – 1:13,520 live births in Germany [2] with an estimated prevalence of 1:20,000 individuals equally distributed among ethnic groups and both sexes. Penetrance and expressivity are variable ranging from mild skin lesions and minimal neurologic signs to severe neurodevelopmental manifestations, including refractive epilepsy, autism spectrum disorder (ASD) and profound intellectual disability (ID) [3, 4]. Mortality is significantly elevated, up to fivefold compared to the general population. The most common causes of TSC-attributable deaths are status epilepticus, sudden unexpected death in epilepsy (SUDEP), kidney complications, and infections. Mortality is especially increased in individuals with ID [5]. About 90% of TSC patients develop neurologic complications, such as epilepsy, ID and ASD [3, 6]. Epilepsy, usually starting during the first year of life, occurs in 83.5% of patients and is the most prevalent and challenging manifestation [3, 7]. Early-onset epilepsy typically presents with focal seizures and infantile spasms (IS). IS or West syndrome is a severe epileptic encephalopathy characterized by epileptic spasms and a pathognomonic EEG pattern (hypsarrhythmia), occurring in 38.8% of affected individuals [7]. Infantile onset epilepsy and in particular IS are suspected to cause alterations in brain maturation with significant impact on neurodevelopment and are considered the most important risk factors for neuropsychologic impairment (ID and ASD) [8]. On the molecular level, TSC is caused by heterozygous loss-of-function variants in the genes *TSC1* and *TSC2*, encoding the Tuberin-Hamartin complex, acting as a critical upstream suppressor of the mammalian target of rapamycin (mTOR), a key signaling pathway controlling cellular growth and metabolism. Haploinsufficiency of *TSC1* or *TSC2* leads to a constitutive activation of the mTOR pathway, resulting in fundamental alterations in neuronal network properties and an imbalance in neuronal excitation and inhibition, acting as a common pathway toward epilepsy, ID and ASD [9, 10]. Therapeutic mTOR inhibition is a promising molecular target for the treatment of TSC-associated manifestations. The mTOR inhibitors sirolimus and everolimus have been increasingly used in TSC and have gained approval for the treatment of TSC-related manifestations, such as subependymal giant cell astrocytomas (SEGA), renal angiomyolipomas and recently, refractory focal epilepsy above the age of 2 years. With respect to neuropsychological manifestation, preliminary trials with mTOR inhibitors in TSC children above 2 years have so far failed to demonstrate beneficial effects. This might be due to the fact that the window of opportunity for the neuromodulatory effects of mTOR inhibitors lies within the first year of life before TSC-related early-onset epilepsy and in particular IS occur as sign of disrupted brain maturation and synaptic formation. Since the influence of mTOR inhibitors on the emerging neuronal network disorder is not fully understood, the exact time at which a therapy has to be started cannot be clearly delineated. Considering the underlying molecular pathomechanisms of TSC and the fact that mTOR inhibitors can reverse many TSC-related manifestations in cell and animal models as well as in anecdotal reports [11-13], it can be hypothesized that pre-emptive initiation of mTOR inhibitor treatment reduces the risk for TSC-related neuropsychologic deficits. To date, there are no published controlled, prospective clinical trials evaluating the effect of pre-symptomatic mTOR inhibitor therapy on neuropsychologic manifestations in TSC patients under 2 years of age.

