Diagnostic Observation Schedule (ADOS) were present in 46% of cases [15]. Similarly, the TOSCA study, the largest natural history study on TSC, reported mild to profound degrees of ID in 55.6% [16]. According to a meta-analysis the burden of disease in TSC is at least twice as high as in the general population. Thereby, children with ID, ASD and epilepsy have a high risk for hospitalization and are more likely to require intensive care treatment [5]. Outpatient visits were even more frequent, due to the high number of specialists that are required in the multimodal care. Quality of life (QoL) is reduced by a high number of neurotropic medications and more diagnostic procedures than in the general population. Global intellectual impairment in TSC is highly correlated to a history of IS and severe intractable seizures [17]. 74.4% of TSC patients with IS develop cognitive impairment in contrast to 39.2% without IS [4, 18]. Furthermore, a higher incidence of ASD is reported in TSC patients with early-onset intractable epilepsy [19]. Antiepileptic treatment has proven to stop IS in 71.5% of cases and showed mitigating effects with respect to ID and ASD [7, 20]. In 2019, Jozwiak and colleagues suggested that pre-symptomatic antiepileptic treatment can reduce occurrence and severity of cognitive impairment in TSC [21]. Recently, the EPISTOP trial published the results of a controlled multicenter study comparing the preventive effect of the antiseizure medication vigabatrin, started after detection of first epileptiform activity on electroencephalography (EEG), versus conventional treatment, on TSC-related epilepsy. The trial showed that preventive treatment was associated with a >2-fold reduction in the risk of drug-resistant epilepsy compared to conventional management. Neurodevelopmental delay at age 2 years was seen in 33% of those on preventive treatment and 50% of those on conventional treatment, however without reaching significance on statistical testing [14]. Two major messages can be derived from this trial. First, the time at onset of epileptiform activity on EEG might be too late for preventive ASD treatment, since aberrant neurophysiological changes that cannot be reversed by treating seizures might have already occurred. Second, isolated antiepileptic treatment with vigabatrin is not sufficient to improve neuropsychologic outcome, highlighting the need for mechanistic and disease modifying therapies. mTOR inhibitors present a promising targeted therapy in TSC and have shown encouraging results in reducing TSC-related epilepsy in patients older than 2 years [22, 23]. Neuropsychologic symptoms were not impacted by treatment, possibly due to the fact that TSC-related implications on brain maturation, laying the structural basis for neuropsychologic impairment, occur before onset of epilepsy [9]. Delayed initiation of mTOR inhibitors might therefore fail to restore cognitive function. There is promising pre-clinical data suggesting that the extent of neuropsychologic impairment in TSC is associated to dysregulated mTOR signaling and that mechanistic treatment with mTOR inhibitors can attenuate some of those symptoms. In *Tsc1* mutant mice depicting abnormal behavior, representative for ASD, mTOR inhibitor treatment starting on postnatal day 7 was able to prevent aberrant neurodevelopment [24]. Additionally, ASD-like phenotypes as well as deficits in learning and memory in *Tsc2* haploinsufficient animal models were reversible with mTOR inhibitor treatment [25, 26]. Clinical trials evaluating these effects in infants and young children remain elusive.

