## 5. Treatment

### 5.1 Measures to minimize Bias

#### 5.1.1 Randomization

Within -14 days prior to study visit V1 and the time of randomization, all required elements of the screening visit will be fully completed and documented by a qualified staff member. For this purpose, informed consent must be obtained from legal guardian(s). The diagnosis of TSC must be confirmed based on the diagnostic criteria. Inclusion criteria and exclusion criteria must be reviewed and documented. Vital signs, physical examination results, EEG, abdominal sonography, and laboratory results must be complete. The results will be entered by a qualified member of the local study team with access to the eCRF. Subsequently, after internal validation, randomization is performed directly via the eCRF at the site on visit 1 and treatment will start at the same day after calculation of the starting dose. The randomization via the eCRF will trigger an email to inform the sponsor and the delegated persons by the sponsor. Eligible patients will be randomized 1:1 to interventional and control arm. Block randomization will be used to minimize the imbalance between the number of patients in each treatment group. While we are expecting no centre effects due to the highly standardized therapeutic management of TSC patients, age at inclusion might bias results. Since the primary endpoint is assessed at two years of age and age at inclusion might vary from 0 to <4 months, the total treatment duration will be different depending on the age at inclusion. Therefore, the randomization will not be stratified by centre but by age groups (0-<2 vs. 2-<4 months of age).

Blinding procedures for the groups are not applicable.

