## 6.2 Screening Visit

During the screening visit (screening and/or V1, week 0) eligibility criteria will be assessed, and an informed consent form (ICF) has to be signed prior to study related procedures. A careful history of the patient's illness, including TSC diagnosis, prior anti-TSC therapy, seizure history and prior ASM use will be assessed. A physical and neurological examination, including assessment of anthropometric data and vital signs, will be taken by an experienced team of trained pediatric neurologists, nurses and physiotherapists. Initial laboratory examinations (hematology, chemistry, lipids, urinalysis) and a screening EEG will be conducted. Patients will then be randomized. In case randomization to the treatment group occurs, caregivers will be instructed on how to administer the study medication and will further be advised to seek immediate medical attention on signs of pneumonia (respiratory distress), recurrent infection or appearance of oral aphthosis, as well as to avoid interacting CYP3A4 inhibitors and inducers. In both study arms, caregivers will receive a seizure diary and will be instructed on how to recognize and count possible prospective seizures and how to complete a daily seizure diary.

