### 9.4 Primary Analysis

As **primary analysis**, the BSID-III cognitive scale of 2 years will be analysed using a two-sided Mann-Whitney-U-test ( $\alpha=0.05$ ) stratified by age groups (0-<2 and 2-<4 months of age) comparing the treatment versus the control group. The Mann-Whitney-U-test is used instead of the t-test because there are hints that the values could be not normally distributed in this

|                                                                    |                                              |                                |
|--------------------------------------------------------------------|----------------------------------------------|--------------------------------|
| Clinical Trial Code: PROTECT
EU trial number: 2022-502332-39-00 | Trial Protocol
(Version 06; (01.10.2024)) | Page 92 of 110
CONFIDENTIAL |
|--------------------------------------------------------------------|----------------------------------------------|--------------------------------|

population. All patients randomized will be evaluated following the treatment policy strategy (ICH E9 R1).

Missing values of patients (including missing values due to early termination of the study) without a BSID-III cognitive scale at the age of 2 years will be replaced

- a) with randomly selected values of patients in the control group (single imputation) if the 1-year value is not available
- b) with data of the control patients using a linear regression model with the 1-year value as independent variable and the 2-year value as the dependent variable (single imputation) if the 1-year value is available

Values of the control group will be used in order to achieve a conservative estimate. No fixed value is used for single imputation (e.g. the median) to reduce the risk to underestimate the variance. The seed to select values randomly is 4421360.

Additionally, the median of the BSID-III cognitive scale and the corresponding 95% CI will be displayed by group.

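### The section 9.7 mixed model and its imputation model leave out seizure, spasm and screening-EEG status at entry, which costs some precision in a sensitivity analysis

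*Protocol*

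**What the plan says.** - **Sensitivity model (9.7).** The primary comparison is repeated "using a linear mixed model with age groups and treatment as fixed factors and site as random factor". For missing scores: "Missing values will be replaced using multiple imputation using age groups and the 1-year value as exploratory variables". No seizure, spasm or EEG term appears in either model.
- **Design and primary test (5.1.1, 9.4).** Randomisation is stratified by age group only. The rank test is likewise "stratified by age groups (0-<2 and 2-<4 months of age) comparing the treatment versus the control group".
- **Risk factors (1.1, 1.2).** Infantile-onset epilepsy, and spasms above all, are "considered the most important risk factors for neuropsychologic impairment". Section 1.2 adds that "74.4% of TSC patients with IS develop cognitive impairment in contrast to 39.2% without IS".
- **Opposing statement (1.3).** No biomarker or prognostic factor is said to be useful for picking out infants at risk, so no stratification is applied on that ground.
- **Data at entry (5.1.1, 5.1.2, 6.2, 6.8).** At screening, seizure history is taken and "a screening EEG will be conducted"; the EEG must be complete before randomisation. EEGs are read centrally by two blinded raters, with epileptiform spikes coded as none, focal or generalised. Seizures at entry are not an exclusion (4.4).
- **Spasms elsewhere (9.8).** The primary analysis is repeated by presence of spasms at randomisation.
- **Room for change (9.3).** The SAP may add analyses, and only changes to the primary analysis need a protocol amendment.

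**The concern.** The mixed model is the only model-based estimate of the treatment difference that the protocol describes. A model of this kind can absorb variation due to a known baseline predictor. The protocol names a candidate, collects it in every child before allocation, and then leaves it out of both the model and the imputation.

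Two things are at stake in a trial of 30 per arm. The first is precision: variation that a baseline factor could explain stays in the residual. The second is interpretation: if the arms happen to differ in the share of children who already have seizures or an epileptiform EEG, no listed analysis returns an overall treatment effect corrected for it. A decision made only after such an imbalance has been seen would be open to challenge.

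**Working it through.** **1. The plan's own power figures.** Table 8 (30 per group, two-sided Mann-Whitney, alpha 0.05) gives >95%, >80%, >62% and >80% for difference/SD of 15/15, 15/20, 15/25 and 11.5/15. The normal formula with n multiplied by 3/π (Mann-Whitney efficiency) gives 96.6%, 81.0%, 62.2% and 82.7%. Simulation (20,000 runs) gives 96.3%, 79.5%, 60.7% and 81.2%. The figures reproduce to within about 2 points and are not in dispute.

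**2. Inputs for the covariate question.**
- n = 30 per arm (4.1); difference 15 and SD 20 (one of the Table 8 scenarios).
- Prevalence p of the factor at entry: not in the protocol. Assumed 5% to 30%. The 39% row below corresponds to the 38.8% in section 1.1, which counts spasms at any time and is an upper reference only.
- Prognostic gap g between children with and without the factor: assumed 10 to 20 points. As a rough guide, if 74.4% versus 39.2% are read as shares below 70 under normality, the gap is SD × (0.656 + 0.274), i.e. about 14, 19 or 23 points at SD 15, 20 or 25. Those percentages concern spasms at any time, so a baseline factor may carry a smaller gap.

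**3. Formulas.**
- SD of the between-arm difference in prevalence = √(2p(1−p)/30).
- One-SD shift of the unadjusted estimate = g × that SD.
- R² = p(1−p)g²/SD²; adjusted residual SD = 20 × √(1−R²).
- Power = Φ(15/(SD × √(2/30)) − 1.96).

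Unadjusted: 15/(20 × 0.2582) = 2.905, so power = Φ(0.945) = 82.8%.

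Low end (p = 5%, g = 10): SD of imbalance 0.056, shift 0.56; R² = 0.0475 × 100/400 = 0.012; power 83.2%.

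High end (p = 30%, g = 20): SD of imbalance 0.118, shift 2.37; R² = 0.21 × 400/400 = 0.21; residual SD 17.8; power 90.5%.

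**4. Results** (chance of imbalance from two independent binomials; ranges are for g = 10 to 20).

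| p | expected children of 60 | arms differ ≥10 percentage points | ≥20 percentage points | one-SD shift (BSID-III points) | adjusted power |
|---|---|---|---|---|---|
| 5% | 3 | 13% | 0.2% | 0.6–1.1 | 83.2–84.5% |
| 10% | 6 | 28% | 1.8% | 0.8–1.5 | 83.6–86.1% |
| 20% | 12 | 42% | 7.5% | 1.0–2.1 | 84.2–88.7% |
| 30% | 18 | 48% | 12% | 1.2–2.4 | 84.7–90.5% |
| 39% | 23.4 | 51% | 14.5% | 1.3–2.5 | 85.0–91.4% |

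**5. Check by simulated linear models** (4,000 runs per scenario, total SD 20, p = 10% to 30%; site and age-group terms omitted). Under no effect, rejection rates were 4.9–5.4% without and 4.6–5.3% with the covariate. With a true difference of 15, the mean unadjusted estimate lay between 14.9 and 15.1. Power went from 80.8% to 80.7% at p = 10%, g = 10 (no gain) and from 81.2% to 88.9% at p = 30%, g = 20.

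**The case against.** The strongest reply is that nothing here is an error. The 9.7 model carries the sole stratification factor and adds site. In a randomised comparison, leaving out further covariates is valid, and the simulations bear that out. Section 9.3 lets the SAP add analyses, so an adjusted model may yet appear. That stands as a limit on weight. It does not remove the point, because the protocol writes out a specific covariate list and a better one is available at almost no cost.

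The second reply concerns timing and also stands in large part. Sections 1.1 and 1.2 mainly describe epilepsy and spasms arising during infancy, and section 1.1 places the treatment window before they occur. Much of that risk therefore appears after randomisation, where it lies on the treatment pathway and must not be adjusted for. No passage says that status at entry strongly predicts the 24-month score. Read this way, section 1.3 need not contradict section 1.1.

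Third, baseline characteristics are tabulated by group, so an imbalance would be visible, and the 9.8 split removes spasm imbalance within each stratum. But that split gives no combined adjusted estimate, ignores focal seizures and EEG findings, and could leave a very small stratum (6 of 60 children at 10%).

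A reader might go further and infer that chance imbalance could supply much of the 5-point observed improvement that section 9.9 regards as enough to carry on. The documents do not support that. The 5 points there are a difference in medians, which changing the 9.7 model would not alter. A shift of 2 to 3 points from a 20-percentage-point imbalance (0.20 × 10 to 15) has a 12% to 14.5% chance only if prevalence at entry is about 30% to 39%. At 5% to 20% the chance is 0.2% to 7.5%, and by symmetry half of any such figure would favour sirolimus.

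**Conclusion.** The point holds as a modest improvement to a sensitivity analysis. The 9.7 model and its imputation model leave out a baseline factor that the protocol's own rationale makes plausible and that is recorded in every child. The cost is some precision and an unadjusted chance imbalance in the one trial that will be run.

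Under the assumed 5% to 30% prevalence and 10- to 20-point gap, a one-SD imbalance is worth about 0.6 to 2.4 points against a target of 15 (2.5 at 39% prevalence). Adjustment is worth about 0.5 to 8 percentage points of power at difference 15 and SD 20. The lower end is negligible, and which end applies depends on an entry prevalence that the protocol does not give.

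It would be wrong to conclude that the trial is biased, that type I error is inflated, that the primary analysis is affected, or that the plan ignores spasms altogether.

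**What to change.** Add one pre-specified binary covariate as a fixed effect in the 9.7 mixed model and as a predictor in its multiple-imputation model: any seizure or infantile spasm before randomisation, or focal or generalised epileptiform spikes on the centrally read screening EEG (yes/no). Use pre-randomisation status only. A single composite is preferable to separate seizure and EEG terms, which are likely to overlap and would be hard to estimate with 60 children and a random effect over some 17 to 20 sites. State in advance what happens if too few children are positive to estimate the term. Leave the primary rank test and the 9.8 subgroup unchanged.

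Under section 9.3 this can be done in the SAP without an amendment, and it should be fixed before outcome data by arm are seen. If the sponsor prefers to keep the current model, one sentence should say why the risk factors of section 1.1 are left out and how that fits section 1.3.

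The cost is one degree of freedom and a short definition. If the factor is rare under 4 months of age, the gain will be close to nil.

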## 9.9 Sample Size/Power Calculation

It seems feasible that 60 patients can be randomized. To randomize 60 patients, 120 patients need to be assessed for eligibility assuming 50% willingness to participate in the trial. Assuming that 30 patients per group can be randomized, a difference of 15 in the cognitive scale of BSID-III at age 2 years will be detectable with a power of >95% using a two-sided Mann-Whitney-U-test ( $\alpha=0.05$  and under normality assumption with a standard deviation (SD) in each group of 15). We consider an improvement of 15 in the cognitive scale of BSID-III at the age of two years (e.g. a score of 75 in the control group and a score of 90 in the treatment group) relevant for reducing neuropsychological impairment, therefore lifting burden of disease and improving social participation and opportunities in school and professional life. The following Table 8 shows the resulting power for 30 patients per group under different assumptions:

Table 8: Power for 30 patients per group under different assumptions

| mean difference | SD per group | power | mean difference considering missing values | SD per group considering missing values | power considering missing values |
|-----------------|--------------|-------|--------------------------------------------|-----------------------------------------|----------------------------------|
| 15              | 15 (a)       | >95%  | ~ 13.5                                     | ~14.7/~15.5                             | >90%                             |
| 15              | 20           | >80%  | ~ 13.5                                     | ~19.7/~20.2                             | >70%                             |
| 15              | 25 (b)       | >62%  | ~ 13.5                                     | ~24.6/~25.1                             | >50%                             |
| 11.5            | 15 (a)       | >80%  | ~ 10.4                                     | ~14.7/~15.2                             | >70%                             |

a) [15, 99] b) [100]

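### The multiple-imputation sensitivity analysis in section 9.7 leaves treatment out of the imputation model, so a real effect is modestly attenuated and the analysis is a poor check on the control-based primary imputation

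*Protocol*

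**What the plan says.** Section 9.7 plans two sensitivity analyses. The first repeats the primary analysis on the per-protocol set. The second repeats it with a "linear mixed model with age groups and treatment as fixed factors and site as random factor", followed by the sentence "Missing values will be replaced using multiple imputation using age groups and the 1-year value as exploratory variables" (the last words presumably mean explanatory variables). Nothing else in section 9 adds treatment to that predictor list or says that imputation is done by arm.

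The primary analysis in section 9.4 handles a missing 2-year score differently. The score is replaced "with randomly selected values of patients in the control group (single imputation) if the 1-year value is not available", and otherwise "with data of the control patients using a linear regression model with the 1-year value as independent variable". The reason given is "Values of the control group will be used in order to achieve a conservative estimate". That reason is attached to the primary single imputation only; section 9.7 gives none for its own imputation model.

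Section 9.9 supplies the planning values: 30 per group, a difference of 15 (for example 75 against 90), SD 15 with 20 and 25 as alternatives, and 10% missing values.

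**The concern.** The factor whose effect is being estimated is in the analysis model but not in the imputation model. The imputed 2-year scores then depend on age group and 1-year score alone, by the same equation in both arms. Two children with the same age group and 1-year score get the same imputed distribution whether or not they were allocated sirolimus. Whatever part of the 2-year effect is not already visible at 1 year is set to zero for them. The estimate is biased towards zero even if data are missing completely at random.

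This matters because of the job the analysis has to do. The primary rule deliberately pulls sirolimus children with missing scores towards control values. If the primary result is weak, the obvious question is how much of that is due to the rule. The mixed-model analysis is the only planned one that keeps all randomised children and handles missing scores differently. If it shrinks the effect in the same direction, agreement between the two is not informative.

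**Working it through.** **Inputs.** From section 9.9: 30 per arm, means 75 and 90 (d2 = 15), SD 15, missing fraction m = 0.10. Assumed, because the protocol does not give them: correlation r between 1-year and 2-year scores, 0 to 0.7; treatment effect at 1 year d1, from 0 (none) through 7.5 (half) to 15 (full); equal missingness in both arms, unrelated to outcome.

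**Step 1: reproduce the plan's own figures (Table 8, first row).**
- Complete data: effective n = 30 × 3/π = 28.65 per arm. z = 15 / (15 × √(2/28.65)) = 3.785, and 3.785 − 1.96 = 1.825, giving power 96.6% (table: >95%).
- With 10% missing and control-based replacement: 0.9×90 + 0.1×75 = 88.5 against 75, a difference of 13.5 (table: ~13.5). Simulation (10,000 runs) gives 13.5 and power 91% (table: >90%).
- The same simulation for the other three rows gives differences of 13.6, 13.4 and 10.3 and power of 71%, 51% and 71%, in line with the table.

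**Step 2: the section 9.7 imputation when the 1-year score carries no treatment information.** Missing scores in both arms centre on the pooled mean (75 + 90)/2 = 82.5.
- Sirolimus: 0.9×90 + 0.1×82.5 = 89.25
- Control: 0.9×75 + 0.1×82.5 = 75.75
- Difference 13.5, a loss of 1.5 (10%)

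**Step 3: the general case.** Scores are drawn from the pooled regression on the 1-year value, which has slope

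b = (r·SD² + d1·d2/4) / (SD² + d1²/4).

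The imputed children retain b·d1 of the effect, so the bias is −m(d2 − b·d1).
- r = 0.5, d1 = 7.5: b = 140.6/239.1 = 0.588; bias = −0.1(15 − 4.41) = −1.06
- r = 0.7, d1 = 7.5: b = 185.6/239.1 = 0.776; bias = −0.1(15 − 5.82) = −0.92
- r = 0.7, d1 = 15: b = 213.75/281.25 = 0.76; bias = −0.1(15 − 11.4) = −0.36

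**Step 4: simulation.** Normal-regression multiple imputation with 10 imputations and Rubin's rules, 1,500 trials per case, linear model with treatment and age group (site omitted), SD 15, 3 of 30 missing per arm:

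| 1-year information | Mean estimate, as written | Mean estimate, treatment added |
|---|---|---|
| No 1-year value used | 13.58 | 15.09 |
| r = 0.5, d1 = 0 | 13.58 | 15.10 |
| r = 0.5, d1 = 7.5 | 13.85 | 14.95 |
| r = 0.7, d1 = 7.5 | 14.09 | 15.03 |
| r = 0.7, d1 = 15 | 14.67 | 15.04 |

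A separate simulation of 3,000 trials per case with r = 0.6 gave biases of −1.58 (no 1-year value), −1.65 (no 1-year effect), −1.02 (half) and −0.50 (full). Formula and simulations together give about 0.3 to 1.6 points. If the same six missing scores all fall in the sirolimus arm, the estimates run from 13.3 to 14.8.

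**Step 5: consequences elsewhere.**
- Power at SD 15: 0.92–0.96 as written, 0.95–0.97 with treatment added. At SD 25: 0.48–0.56 against 0.57–0.59.
- At 20% missing per arm, SD 15: 12.0–14.4 as written, 15.0–15.1 with treatment added.
- No true effect, 10% missing per arm: no bias in either version; rejection rate about 2.5–5% as written.

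**The case against.** Four stronger readings are tempting, and the protocol does not support them.

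- **That this is the only planned analysis free of control-based imputation.** It is not. Under section 9.1 the per-protocol set contains only children who completed the 2-year test, so the per-protocol repeat has no imputed 2-year score. It gives partial information on the same question. It also selects on at least 9 months of treatment, so it changes the population along with the missing-data handling. What remains true is that the mixed-model analysis is the only all-randomised alternative.
- **That imputed scores go to the pooled mean.** This holds only when the 1-year score is uninformative about treatment. Otherwise they go to the pooled regression, and a 1-year score that already shows the effect reduces the bias to about 0.3 points.
- **That adding treatment removes all bias at no cost.** That is so only if data are missing at random within arm. Section 9.4 follows a treatment-policy strategy, and section 7.2 lets children who stop sirolimus stay in follow-up, so those without a 2-year score may largely be children who left the trial and are off drug. Suppose the missing sirolimus children truly average 75. The policy difference is then 0.9×90 + 0.1×75 − 75 = 13.5. The model as written gives 13.5 and the corrected model gives 15, an excess of 1.5. The exact match is a product of the chosen scenario, but the point stands: adding treatment changes the assumption and must be declared as such.
- **That the trial's main conclusion is at risk.** The primary test does not use this model.

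It can also be said that section 9.3 leaves detail to the SAP and allows changes outside the primary analysis to be made there alone. That lowers the urgency. It does not remove the point, because section 9.7 gives a definite predictor list and programming to it would reproduce the problem. Nor can the omission be read as deliberate caution, since no such reason is given for it.

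**Conclusion.** The point holds as a moderate defect in a sensitivity analysis. Under data missing at random, a true effect of 15, SD 15 and 10% missing, the estimate is attenuated by about 0.3 to 1.6 points (roughly 2 to 11% of the effect), depending on the assumed 1-year effect and correlation. The attenuation grows with more missing data. Under no true effect there is no bias and no inflation of type I error.

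The practical loss is interpretive. At worst the analysis shrinks the effect to the same 13.5 or so as the primary rule, so it cannot cleanly separate a weak treatment effect from the effect of control-based imputation.

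**What to change.** In section 9.7, or in the SAP as section 9.3 allows, add treatment group to the imputation model alongside age group and the 1-year score, or impute separately within arm. Impute missing 1-year scores in the same model.

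Add a sentence stating that this analysis assumes missing at random within arm, that it may favour sirolimus if children without a 2-year score had stopped treatment, and that the control-based primary analysis is its conservative counterpart. If leaving treatment out was intended, say so and label the analysis as conservative.

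The cost is one model term and a sentence or two of text. No new data are needed and the primary analysis does not change.
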